### Intervention: iSupport

iSupport is an online support program used to enhance self-care skills and support carers of people with dementia. The intervention has been developed by the WHO in collaboration with international experts in the field and Alzheimer Disease International. Final content decisions of the generic version were based on the outcomes of focus groups with professionals and unpaid carers, a pilot study (N=10) in India, and discussion within the project group. iSupport is based on the principles of CBT and includes techniques such as problem solving, relaxation, and cognitive reframing. During the development of the intervention, ethical principles and the needs of the carers were considered.

iSupport consists of 23 lessons distributed over five modules: (1) What is dementia? (one lesson), (2) Being a caregiver (four lessons), (3) Caring for me (three lessons), (4) Providing everyday care (five lessons), and (5) Dealing with challenging behavior (10 lessons). In Table 1, an overview of the topics covered through all modules and lessons is presented.

Carers may pick and choose which lessons they would like to do, depending on their needs and how relevant the topic of the lesson is to them. Every lesson follows the same format, consisting of information about the main topic of the lesson; small exercises, after which participants receive instant personalized automated feedback; and a summary of the lesson plus a relaxation exercise. In order to personalize the feedback and the content of the intervention, participants are asked to provide their own name, the name of the person with dementia, their relationship, and some other basic demographics (ie, gender and age). The program can be followed via the internet on a personal computer or tablet.

**Table 1 table1:** Modules and lessons from iSupport.

Modules	Lessons
1. What is dementia?	1.1. Introduction to dementia
2. Being a caregiver	2.1. The journey together 2.2. Communication 2.3. Shared decision making 2.4. Involving others
3. Caring for me	3.1. Reducing stress in everyday life 3.2. Pleasant activities 3.3. Thinking differently
4. Providing everyday care	4.1. Eating and drinking: more pleasant mealtimes 4.2. Eating and drinking: preventing health problems 4.3. Toileting and continence care 4.4. Personal care 4.5. Enjoyable day
5. Dealing with challenging behavior	5.1. Introduction to challenging behaviors 5.2. Memory loss 5.3. Aggression 5.4. Depression and anxiety 5.5. Difficulty sleeping 5.6. Delusions and hallucinations 5.7. Repetitive behaviors 5.8. Walking and getting lost 5.9. Poor or decreased judgement 5.10. Putting it all together

Participants will be advised to use the iSupport program regularly to benefit as much as possible from their participation. It is anticipated that carers will be able to complete the whole program in 3 months. Participants will be able to indicate that they want some personal contact by sending their email address to our e-coaches. They will then be contacted by an e-coach three times via email: right after the first email, 1 month later, and 2 months later. Additionally, carers may contact the e-coach, if necessary, at any point of the intervention, although we aim not to have more than 10 interactions between e-coaches and participants. The purpose of the e-coach is to encourage participants to continue with the iSupport program, to explain anything that is not clear to the carer in the iSupport program, and to help to find additional support if needed. The emails that are sent by the users will be anonymized and used to improve the iSupport program. The coaches will be volunteers currently working for the telephone helpline of AN. They will complete a 4-hour training session by members of the research team in order to fully comprehend the intervention and the study.

The generic iSupport intervention is in English. However, during the developmental stages, attention has been paid to the possibility of adapting the intervention to different languages and cultural and economic situations. We adapted the generic version to the Dutch context. This means that the intervention has been translated by an official translator, who is knowledgeable in the field of dementia care, following the adaptation and implementation guide provided by the WHO. All text not pertinent to Dutch culture has been adapted (ie, names, activities, timetables, email addresses, etc). Afterward, the text was reviewed by staff of AN and an independent reviewer to ascertain that the adaptation was accurate and a dementia-friendly vocabulary was used.

### Intervention: Waiting List Control Group

Participants assigned to the waiting list condition will receive access to the iSupport intervention 3 months after the baseline session. We will stress that carers allocated to this group will be allowed to access any help they may need from online resources, to participate in support groups, or to access any type of professional help.

### Assessments

All assessments will be administered online and consist of a variety of self-reported measures. During the first measurement, we will assess the inclusion and exclusion criteria. Only those people that are eligible will complete the remainder of the baseline questionnaires. Table 2 provides an overview of the questionnaires and the number of items for each assessment.

### Primary Outcome

Our primary outcome is perceived stress. Perceived stress will be assessed with the PSS [25]. The PSS is a 14-item scale designed to measure global levels of stress and to assess to what extent participants perceive their lives as unpredictable, uncontrollable, and overloaded. Each item is scored on a Likert-type scale from 0 (never) to 4 (very often). The total score ranges from 0 (no stress) to 88 (very stressed).

**Table 2 table2:** Overview of measures.

Collected data and instrument			Outcome measures	Items, n	T0^a^	T1^b^	T2^c^
**Demographic data of carers and persons with dementia**							
	Sociodemographic questions		Age, gender, etc^d^	15	x^e^	N/A^f^	N/A
**Inclusion criteria**							
	Burden scale		Caregiver burden	1	x	N/A	N/A
	AD8^g^		Functional decline	8	x	N/A	N/A
**Primary outcome**							
	PSS^h^		Perceived stress	14	x	x	x
**Secondary outcomes**							
	**Mental health**						
		CES-D^i^	Depression	20	x	x	x
		HADS-A^j^	Anxiety	7	x	x	x
		ZBI^k^	Caregiver burden	12	x	x	x
	**Mastery and sense of competence**						
		PMS^l^	Mastery	7	x	x	x
		RIS^m^ Elder Care Self-Efficacy Scale	Self-efficacy	10	x	x	x
		SSCQ^n^	Sense of competence	2	x	x	x
	**Attitude toward dementia and the care recipient**						
		ADQ^o^	Approaches to dementia	11	x	x	x
	**Treatment adherence, usage, and satisfaction**						
		SUS^p^	Usability	10	N/A	x	N/A
		Postlesson questions	Satisfaction	2 per lesson	N/A	x	N/A
		Analysis of platform data	Intervention usage	N/A	N/A	x	N/A

^a^T0: baseline assessment.

^b^T1: 3-month follow-up assessment.

^c^T2: 6-month follow-up assessment.

^d^Demographic data of carers: age, gender, marital status, number of children, children living at home, relationship with the person with dementia, level of education, months of caregiving, and average days per week providing care. Demographic data of persons with dementia: age, gender, marital status, living situation, and diagnosis.

^e^The questionnaire is included at the questionnaire battery for the different time points (T0, T1, T2), in opposition to N/A.

^f^Not applicable.

^g^AD8: Ascertain Dementia 8-item informant questionnaire.

^h^PSS: Perceived Stress Scale.

^i^CES-D: Centre for Epidemiological Studies Depression scale.

^j^HADS-A: Hospital Anxiety and Depression Scale-Anxiety subscale.

^k^ZBI: Zarit Burden Interview.

^l^PMS: Pearlin Mastery Scale.

^m^RIS: relational self-efficacy, instrumental self-efficacy, and self-soothing efficacy.

^n^SSCQ: Short Sense of Competence Questionnaire.

^o^ADQ: Approaches to Dementia Questionnaire.

^p^SUS: System Usability Scale.

### Secondary Outcomes

Our secondary outcomes are related to (1) mental health (ie, symptoms of depression, anxiety, and caregiver burden); (2) mastery and sense of competence; (3) attitude toward dementia and the care recipient (ie, person-centered approach); and (4) intervention usability, intervention use, and satisfaction with the content of the intervention.

Anxiety symptoms will be measured using the Dutch version of the HADS-A. The HADS-A [26] consists of seven items concerning anxiety complaints experienced in the past week. Subjects will score these feelings on a 4-point Likert scale from 0 (not at all) to 3 (nearly every day); the total score will range from 0 (no anxiety) to 21 (many anxiety symptoms).

Depressive symptoms will be measured with the CES-D [27]. This Likert-type scale consists of 20 items for which subjects will rate the frequency of symptoms during the past week. Scores range from 0 (rarely present or present none of the time: less than one day) to 3 (present most or all of the time: 5-7 days). The total score will range from 0 (no depression) to 60 (very depressed).

Perceived caregiver burden will be measured with the 12-item Zarit Burden Interview (ZBI) [30,31]. The scale measures a number of different types of burden, including the emotional, social, and financial impact of caring for someone. Each of the 12 items will be scored on a 5-point Likert scale from 0 (never) to 4 (nearly always). The total score will range from 0 (no burden) to 48 (very high burden).

Mastery will be measured using the 7-item Likert-type Pearlin Mastery Scale (PMS) [32,33]. The item scores range from 1 to 5, hence, the total scale score will range from 7 to 35. A high score represents internal mastery and indicates that someone has the feeling of being in control of situations. A low score represents external mastery and indicates that someone has the feeling that things are outside of their control.

Next, we will measure the feelings of self-efficacy with the relational self-efficacy, instrumental self-efficacy, and self-soothing efficacy (RIS) Elder Care Self-Efficacy Scale [34]. This scale measures the extent to which someone believes they are able to successfully master a specific task [35]. The scale consists of three subscales: (1) relational self-efficacy (three items): beliefs about one’s ability to maintain a cooperative and harmonious relationship with the recipient of care, (3) instrumental self-efficacy (four items): beliefs about one’s ability to accomplish tasks associated with the provision of personal care, and (3) self-soothing efficacy (three items): beliefs about one’s ability to maintain their own well-being in the midst of emotionally taxing and usually unrelenting demands. Each of the 10 items is rated on a 5-point Likert scale ranging from 1 (I’m certain I can’t do this) to 5 (I’m certain that I can do this). The subscale scores are derived by summing the item scores. Higher scores indicate increased self-efficacy.

We will measure sense of competence using the Short Sense of Competence Questionnaire (SSCQ) [36], which consists of seven items, five of which are already included in the ZBI. This means that we will ask participants to address the two remaining items. Three domains are distinguished in the SSCQ: (1) satisfaction with the person with dementia as a recipient of care, (2) satisfaction with one's own performance as a carer, and (3) consequences of involvement in care for the personal life of the carer. Each item is scored on a 5-point Likert scale, ranging from 1 (agree very strongly) to 5 (disagree very strongly). The total score will be derived by summing up the item scores.

The relationship between the carer and the person with dementia will be assessed with one of the subscales from the Approaches to Dementia Questionnaire (ADQ) [37]. This 11-item subscale measures *recognition of personhood*. This reflects the extent to which people have a person-centered understanding of dementia. It assesses to what extent the carer recognizes the care recipient as a unique and valuable individual. Each item will be answered on a 5-point Likert scale ranging from 1 (completely agree) to 5 (completely disagree). The total score will be a summation of the item scores and will range from 11 to 55. Higher scores will indicate more positive attitudes regarding personhood toward people with dementia.

We will use the 10-item System Usability Scale (SUS) [38] to evaluate the overall usability of the iSupport program. This questionnaire was specifically developed to evaluate information and communications technology products, websites, and applications. Each item is a statement and the respondent will need to indicate to what extent they agree with the statement on a 5-point Likert scale, ranging from 0 (strongly agree) to 4 (strongly disagree). An example of a statement is “I thought iSupport was easy to use.” The total score will range from 0 to 40 and will be multiplied by 2.5 to convert the scores to 0-100.

We will gather data about participant satisfaction from the completed lessons: after every lesson, carers will be asked two questions about how satisfactory the lesson was for them. The use of iSupport will be assessed by downloading track-and-trace data. We will examine the number of log-ins, the total time spent on the intervention, and the number of completed lessons.

Finally, we will also gather information on sociodemographic variables. For carers, we will collect information on the following: age, gender, relationship to the person they are caring for, civil status, level of education, average hours of care per week, and living arrangements (ie, cohabiting or not with the person they are caring for). For the person with dementia, we will collect information on the following: age, gender, existence of an official diagnosis, type of dementia, and time since the diagnosis was given.

### Sample Size

Perceived stress is our primary outcome measure and is used for the power calculation. Based on the results of a previous study about an online intervention for carers [39], we expect an effect size (Cohen *d*) of 0.40. Assuming an alpha of .05 and a statistical power (1-beta) of .80 in a two-tailed test, we will need 100 respondents in each of the conditions, resulting in a total of 200 participants. Calculation of the sample size was carried out with G*Power 3.1.9.2 (Heinrich-Heine-Universität Düsseldorf) [40].

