**Methods:**

A superiority two-arm RCT comparing the effects of the online support program with a waiting list control condition will be carried out in the Netherlands. The iSupport intervention was developed by the World Health Organization and is based on cognitive behavioral therapy principles. It has five main themes divided into 23 lessons. Carers can pick and choose which lessons they want to complete. We aim to recruit 200 unpaid carers. The experimental group (n=100) will be provided with access to the intervention for 3 months following randomization; those in the waiting list control group (n=100) will be granted access to the intervention after 3 months. Assessments will be conducted at baseline (T0), 3 months after baseline (post intervention, T1), and 6 months after baseline (follow-up, T2). The primary outcome is perceived stress, measured by the Perceived Stress Scale. Secondary outcomes are symptoms of depression and anxiety, caregiver burden, sense of competence, self-efficacy, mastery, and carers’ attitudes toward dementia and their person-centered approach (ie, to what extent carers tailor the provided care to the interest, needs, and history of the person with dementia).

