### Randomization and Blinding

A randomization schedule with a 1:1 allocation ratio will be made with a computerized random number generator using variable block sizes of two and four by an independent researcher. We will stratify for gender and for the type of relationship between the carer and the person with dementia (ie, partner or other). After every inclusion, the same independent researcher will reveal the next randomization outcome so that allocation is concealed. Participants will be informed about the randomization outcome by email.

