## Discussion

In this paper, we outlined the design of an RCT to examine the effectiveness of iSupport for families and other unpaid carers of people with dementia in improving their mental health and coping strategies.

iSupport was developed by the WHO for global implementation and therefore includes guidelines for translation and cultural adaptation of the intervention. Internet interventions are a promising channel to prevent or treat mental health conditions of relatives and other unpaid carers who face greater risk of experiencing mental health problems themselves [41]. iSupport may increase unpaid carers’ worldwide accessibility to the support they need through the internet. An advantage of the intervention is that it is flexible and carers can decide which lessons they want to complete. Another advantage is that it can be provided with no or minimal professional support. This enables upscaling of the intervention without high costs. It might fit into a stepped-care model, in which only the carers who need more support are stepped up to face-to-face interventions. Additionally, family and other unpaid carers go through different stages during the course of dementia; their needs and preferences for training and support may substantially vary accordingly [42,43]. iSupport contributes to enriching and completing a continuum of interventions addressing the needs of carers in the Netherlands. This continuum should cover interventions from face-to-face to online interventions as well as guided to self-help interventions and everything in between.

The fact that the intervention is offered with minimal support might not only be a strength but also a weakness. It might lead to higher dropout rates. A review on the treatment adherence of online interventions carried out in 2008 [44] shows that in some trials participants never accessed the interventions tested, while others used them inconsistently. We try to minimize that risk by providing personalized automated feedback in iSupport as well as via periodic contact with e-coaches and the option to consult the e-coach more frequently. Hopefully, this encourages carers to continue with the intervention.

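### The 80% power figure needs 100 evaluable carers per arm, and exactly 100 per arm are recruited, so the stated calculation has no margin for the dropout the plan itself provides for

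*Protocol article*

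**What the plan says.** The Sample Size section bases the calculation on perceived stress, the primary outcome. From an earlier online carer study, "we expect an effect size (Cohen *d*) of 0.40". The error rates follow: "Assuming an alpha of .05 and a statistical power (1-beta) of .80 in a two-tailed test". The conclusion is that "we will need 100 respondents in each of the conditions, resulting in a total of 200 participants". The section makes no allowance for attrition.

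The Methods paragraph of the abstract uses the same figure as the recruitment target: "We aim to recruit 200 unpaid carers". It then gives both arms at randomisation: "The experimental group (n=100) will be provided with access to the intervention for 3 months following randomization" and "those in the waiting list control group (n=100) will be granted access to the intervention after 3 months". The Randomization and Blinding section confirms equal allocation ("A randomization schedule with a 1:1 allocation ratio").

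The Statistical Analysis section provides for loss. It plans a comparison of carers who leave the study with those still in it at 3 months, a sensitivity analysis restricted to carers with both pretest and posttest questionnaires, and a missing-data method to be chosen from the amount and pattern of missingness. The primary model is a GEE on change in Perceived Stress Scale (PSS) scores, with baseline correction only if the arms turn out unbalanced at baseline. On the consequence of minimal support, the Discussion adds: "It might lead to higher dropout rates".

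**The concern.** A sample size from a two-sample test is the number of people whose outcome enters the comparison. Here the same number is also the number randomised. Every missing T1 score therefore takes the trial below the number that the calculation says it needs, and the document prepares for missing T1 scores in its analysis but not in its sample size.

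What is at stake is the power statement. If the result is not significant, readers will take it as coming from a trial with an 80% chance of detecting d = 0.40. The calculation as printed supports that only if almost everyone returns the T1 questionnaire.

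**Working it through.** **Inputs from the protocol article.** d = 0.40, two-sided alpha = 0.05, power = 0.80 (Sample Size); 100 randomised per arm (abstract, Methods); 1:1 allocation (Randomization and Blinding). **Not in the document, so assumed as ranges:** loss of T1 scores, and the baseline-to-T1 correlation r of the PSS.

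**1. Reproduce the stated figure.** Normal approximation:

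n per arm = 2(1.960 + 0.842)² / d² = 2 × 7.85 / 0.16 = 98.1, so 99.

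The exact noncentral t calculation gives 99.08, rounded up to 100. Power with 100 evaluable per arm is 0.804. The plan's 100 per arm is reproduced.

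**2. Margin.** 1 − 99.08/100 = 0.009, so the stated calculation can lose 0.9% of T1 scores before power falls below 0.80.

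**3. Power of the stated calculation after loss.** Evaluable n per arm = 100 × (1 − loss). Power comes from the noncentral t with noncentrality 0.40 × √(n/2). Detectable d is the effect with 80% power at that n.

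| Assumed T1 loss | Evaluable per arm | Power at d = 0.40 | Detectable d, 80% power |
|---|---|---|---|
| 0% | 100 | 0.80 | 0.40 |
| 5% | 95 | 0.78 | 0.41 |
| 10% | 90 | 0.76 | 0.42 |
| 20% | 80 | 0.71 | 0.45 |
| 30% | 70 | 0.65 | 0.48 |
| 40% | 60 | 0.58 | 0.52 |

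**4. Does the planned model change this?** The GEE is not an unadjusted posttest t test, so two approximations are worth setting out. Both take d = 0.40 as standardised on the posttest SD.

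*Baseline PSS always in the model:* effective d = 0.40/√(1 − r²), which is 0.419 at r = 0.3 and 0.462 at r = 0.5.

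| Assumed T1 loss | r = 0.3 | r = 0.5 |
|---|---|---|
| 10% | 0.80 | 0.87 |
| 20% | 0.75 | 0.83 |
| 30% | 0.69 | 0.77 |
| 40% | 0.63 | 0.71 |

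The loss at which power falls to 0.80 is about 10% for r = 0.3 and about 25% for r = 0.5.

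*Raw change scores:* effective d = 0.40/√(2(1 − r)). At r = 0.5 the divisor is 1, so there is neither gain nor loss against step 3.

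| Assumed T1 loss | r = 0.4 | r = 0.5 | r = 0.6 | r = 0.7 |
|---|---|---|---|---|
| 10% | 0.68 | 0.76 | 0.85 | 0.93 |
| 20% | 0.63 | 0.71 | 0.80 | 0.90 |

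So the same loss can leave power below or above 0.80, depending on r and on how baseline is handled.

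**The case against.** **The sum is correct.** It is. This is not an arithmetic error. The defect is that a requirement for analysed carers is used unchanged as a recruitment target.

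**The Discussion does not predict study dropout.** A reader might infer that the authors expect substantial loss. The text says only that dropout might be higher. What follows is mainly about people not using an online programme, together with measures to reduce that. Under intention to treat, a carer who stops using iSupport but returns the T1 questionnaire still counts. This objection stands, and the Discussion is weak support. The point rests instead on the Statistical Analysis section, which refers to study dropouts at 3 months, a completers analysis and missing data.

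**Power may be fine under the planned model.** A reader might also infer that 80% power holds only with zero loss, or that the design certainly falls short of it. The document supports neither. The first is essentially true of the unadjusted two-sample test but not of every analysis: step 4 shows power above 0.80 at 20% loss if r is high enough and baseline is used well. It also shows power well below 0.80 when r is low and change scores are analysed. The document gives no correlation and makes baseline adjustment depend on observed imbalance, so the printed 0.80 cannot draw on that gain. Intention to treat and GEE do not otherwise restore the information lost with missing T1 scores.

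**The size is assumed.** True. No dropout rate appears, the upper end of the range has no basis in the document, and at 5% loss the shortfall is only about 2 percentage points (0.78).

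**The article condenses a fuller protocol.** Reasoning about attrition could sit there, but the stated inputs already use up all 200, so no hidden allowance fits within the published numbers.

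**Conclusion.** The point holds in a limited form. The stated power of 0.80 belongs to 100 evaluable carers per arm, while 100 per arm is the number recruited, in a plan that provides for study dropouts. That the stated calculation has a margin below 1% follows from the document alone. The size of the shortfall does not: it rests on the assumed T1 loss, and at 20% loss the type II error of the stated calculation is 0.29 where 0.20 is claimed. The power of the GEE actually planned cannot be determined from the document. The sample size was computed correctly and the trial can proceed with it. What needs correcting is the power statement.

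**What to change.** Keep the total of 200. In the Sample Size section, state the team's own expected loss of T1 PSS scores, and give power at d = 0.40, or the detectable d at 80% power, for the resulting evaluable number per arm, with a range around that loss. Step 3 supplies the values. The percentages used there illustrate the calculation and should not be copied as if they were the trial's expectation.

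Quote a baseline-adjusted power only if the Statistical Analysis section is changed as well, so that baseline PSS is always in the primary model and not only when the arms look unbalanced. In that case state the assumed correlation, its justification and a range: at 20% loss, for example, 0.75 with r = 0.3 and 0.83 with r = 0.5. Without that change, an adjusted figure would describe an analysis to which the plan does not commit.

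The cost is one or two sentences and a somewhat less favourable power statement. Recruitment, already at 120 in July 2019, is unaffected.
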